### Data collection

Anthropometric, behavioral, psychosocial and physiological outcomes will be evaluated at baseline, immediately following the 12-week intervention, and at follow-up (24 weeks). At each of these time points, weight will be measured using an electronic calibrated scale (Seca 876, Chino, CA) and rounded to the nearest 0.1 kg with participants wearing light clothing and no shoes. Height will be measured by a portable stadiometer (ShorrBoard, Olney, MD) and rounded19 to the nearest 0.1 cm. Waist circumference, linked to metabolic syndrome in children [34], will be measured at the umbilicus using standard protocols [35]. All anthropometric measures will be taken in duplicate and averaged. Lacking a gold standard for measuring change in weight status in children, we will use the recommended change in percentage overweight [36] calculated as percentage over the median BMI for age and gender. Child dietary intake will be assessed using two non-consecutive, 24-hour dietary recalls collected by trained nutritionists and entered into Nutrient Data System for Research (Minneapolis, MN, v. 2012) [37] Changes in physical activity will be measured over a 7-day period using Actigraph GT3X accelerometers (Actigraph, Pensacola, FL); raw accelerometer counts will be processed and analyzed using youth-specific cut-points [38].

Psychosocial measures will be evaluated to assess mediators of behavior change using validated questionnaires for youth including self-efficacy related to nutrition [39, 40] and physical activity [41], perceived competence in maintaining a healthy diet and exercising regularly [42], and perceived parental support [43]. Parents/caregivers will complete the Family Nutrition and Physical Activity Screening Tool [44] designed to assess environmental support for healthy eating and activity (e.g. provision of nutritious food and opportunities to be physically active), and will also self-report food parenting practices using the Comprehensive Feeding Practices Questionnaire [45]).

Physiological outcomes will be assessed through 12-hour fasting insulin, glucose, and lipids drawn at J2 Laboratories, Tucson, Arizona, by a trained phlebotomist and placed into serum separator vacuum tubes. Insulin resistance (IR) will be assessed using HOMA [46], shown to more sensitive for identifying youth with metabolic dysregulation than an impaired fasting glucose threshold [47]. Calculation of IR is based on modeling of fasting insulin and glucose concentrations using the formula: fasting insulin (μU/ml) × fasting glucose (mmol/L)/22.5 = HOMA. HOMA correlates closely to IR as measured by euglycemic clamp [48], and a HOMA insulin resistance value of 2.6 will be used as the upper limit of normal [49]. Blood pressure will be measured on the non-dominant arm using an automatic monitor (Omron HBP-1300, Hoofddorp, The Netherlands) and cuff-sizes appropriate for the mid-upper arm circumference. Systolic and diastolic blood pressure will be measured two times with 5 min intervals while the participant is seated and resting. The definition of hypertension will be adjusted for age per national guidelines [50]. Individuals with fasting glucose values >126 mg/dL and no previous history of T2D will be referred to their primary care provider. The study medical director will be immediately informed and arrange appropriate follow-up depending on the level of blood glucose elevation and symptoms. Maturity will be assessed using Tanner’s validated self-report questionnaire which presents illustrations of developmental stages shown to agree with pubertal staging by a physician [51, 52].

Feasibility data will include recruitment, enrollment, and retention rates, program attendance and engagement, and delivery costs. Program satisfaction will be self-reported by participants (parents and children) using brief surveys that inquire about relevance of content, promoters and barriers to attendance and engagement, and degree to which the family applied the intervention to lifestyle behavior changes. Adherence data will include attendance logs and time spent with mobile content (hybrid condition), and completion of self-monitoring and goal-setting activities (both conditions). Importantly, our mobile infrastructure [28] permits capture of engagement with mobile lessons including frequency and duration of participant log-ins, communication with lifestyle coaches, and content downloads/views, which will allow us to characterize engagement and associated it with adherence metrics.

### Data collection

Data collection and entry, and statistical analyses will be conducted by research staff who are blinded to treatment allocation. Participants will be assigned a study identification number upon enrollment. Study personnel involved in data collection will follow a strict written protocol that describes study measures for protecting confidentiality and privacy. All aspects of data collection and storage will be carefully monitored to ensure rapid detection of errors, inconsistencies or other problems. Data will be double entered with third party verification to insure data integrity, and kept in locked files and on a dedicated study computer and secure network. Access will be restricted to the principal investigator and designated staff. Files with information linking names and other personal data to participant identification numbers will be deleted at the end of the study, and written copies will be shredded.

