## Methods/Design

### Study design

The impact of the EPIC Kids intervention will be evaluated using a group-randomized, non-inferiority trial design with three data collection points: baseline, post-intervention (immediately post program completion at 12 weeks), and follow-up (24 weeks) (Fig. 1). The program will be tested with sixty, 9- to 12 year-old children and their parent(s) or primary caregiver(s) at two YMCA locations in Tucson, Arizona where families lack services and resources needed for T2D prevention. Randomization to delivery formats will occur by YMCA location to minimize between-group contacts. One site will conduct a face-to-face weekly YMCA lifestyle coach-led program, while the second site will host a program equivalent in duration, frequency, and content, also lead by YMCA coaches, but with 5 weeks (40 %) of content digitally delivered using study-provided mobile devices (Kindle Fire HDX7, Amazon). Thirty families will be recruited to participate in each intervention format; each family will be assigned to an intervention group led by two trained YMCA lifestyle coaches and consisting of up to 9 other families. Weekly sessions will occur over 1.5 h for 12 weeks.

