### Sample size and power

The primary outcome is change in percent overweight. Our estimated sample size was informed by the results of Foster et al. [18] who observed a mean decrease of 4.3 % in percentage overweight (SE = 1.1) in a YMCA-based pediatric obesity intervention over 6 months, and is based on the number of participants needed to detect an effect size of this magnitude with 80 % power assuming a one-sided test at alpha = 0.05. Given a final sample of 48 children and allowing for up to 20 % attrition, 60 participants will be recruited.

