### Research setting

The YMCA of Southern Arizona (YMCA-SAZ) will play a significant role in the intervention. As a certified training center for the Y-USA Diabetes Prevention Program (YDPP), YMCA-SAZ administrators and staff have experience delivering the successful adult-focused YMCA Diabetes Prevention Program [8, 16]. Two sites will serve as study locations, at which intervention and assessment activities will be conducted. Both facilities are easily accessible by public transit. Membership demographics indicate substantial minority and underserved membership (~67 % Hispanic, 71 % eligible for free and reduced lunch). Both locations report high family memberships (in the hundreds). Standard amenities at all YMCA locations include full service childcare available to all members free of charge; community rooms and free Wi-Fi throughout; sports fields; cardio wellness centers with state-of-the-art strength and fitness equipment; group exercise facilities; a complete aquatics center; locker rooms; and a space dedicated to youth activities. In addition, both YMCA locations provide sports, recreation, and fitness activities tailored to families. YMCA family memberships will be provided free of charge to all participants for the duration of the study.

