## Procedures

### Randomization

Two YMCA sites, [A] and [B], were randomly assigned to face-to-face versus hybrid intervention formats using a random number table. Based on alphabetical order and an even number selected, [A] was assigned to receive the face-to-face format and [B] was assigned the hybrid format.

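### On-site assessors cannot credibly be called blinded to delivery format, because format is fixed by site and children are assessed at those sites

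*Protocol article*

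**What the plan says.** The article has two sections headed Data collection. The second makes the blinding claim, without qualification and for three groups of staff at once: "Data collection and entry, and statistical analyses will be conducted by research staff who are blinded to treatment allocation".

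Other sections describe the setting in which this has to hold:

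- **Study design:** "Randomization to delivery formats will occur by YMCA location to minimize between-group contacts".
- **Randomization:** there are two sites. Site A received the face-to-face format and site B the hybrid format.
- **Research setting:** "Two sites will serve as study locations, at which intervention and assessment activities will be conducted".
- **First Data collection section:** bloods are the stated exception to on-site assessment. "Physiological outcomes will be assessed through 12-hour fasting insulin, glucose, and lipids drawn at J2 Laboratories, Tucson, Arizona, by a trained phlebotomist".
- **Sample size and power:** "The primary outcome is change in percent overweight". The first Data collection section derives it from measured weight and height.
- **Statistical analysis:** the 12-week change is tested with a one-sided paired t-test that pools both formats. The comparison of formats is exploratory and acknowledged to be underpowered.

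**The concern.** With one format per site and measurement at the site, anyone who measures a child there knows the only fact needed to identify the format. The sentence therefore credits the design with a property it does not appear to have for the staff who take the primary measurements.

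Two things are at stake. A reader may treat the on-site outcomes as blinded assessments. A reader may also carry that credit over to the headline pre-post result, where blinding to format would offer little protection even if it were complete.

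**Working it through.** The protocol gives no figure on this point, so the check sets the sections side by side and then asks what format masking could protect.

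**Step 1. Does site reveal format?** Two sites, two formats, one format each (Study design; Randomization). Site and format are the same variable.

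**Step 2. Who knows the site?**

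| Group named in the blinding sentence | Where they work, per the article | Can masking to format hold? |
|---|---|---|
| On-site data collectors (height, weight, waist) | At the two intervention sites (Research setting) | Not credibly; no means is described |
| Blood sampling and assays | Outside laboratory (first Data collection section) | Feasible |
| Data entry | Not stated; participants carry study ID numbers | Feasible with coded IDs and site codes |
| Analysis | Not stated | Feasible with site codes, if mobile-use records are kept apart |

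The condition in the last row follows from the first Data collection section: time spent with mobile content is recorded for the hybrid condition only, so those records show the format.

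**Step 3. What would format masking protect?** Let *c* be a measurement shift in the 12-week change common to both sites, and *d* an extra shift at one site caused by assessors' expectations about its format. Thirty families per site and 20% attrition give 30 × 0.80 = 24 children per site, 48 in all (assuming equal loss at the two sites).

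- Bias in the between-format difference = *d*.
- Bias in the pooled mean change = *c* + *d* × 24/48 = *c* + *d*/2.

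Perfect masking to format sets *d* to zero and leaves *c* untouched. Because every child is treated and there is no untreated comparison group, *c* passes in full into the primary result.

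**Step 4. Illustration for *c* only (all inputs assumed).** Take true change zero, n = 48, a one-sided paired t-test at 0.05, and noncentrality *c*√48/SD. The article gives neither the SD nor the n behind its SE of 1.1, so two SDs are shown. The larger is close to the SD at which 48 children give 80% power: 4.3 × √48 / (1.645 + 0.842) = 12.0 by the normal approximation.

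| Assumed common shift *c* (percentage points) | Type I error, SD 12 | Type I error, SD 8 |
|---|---|---|
| 0.5 | 0.09 | 0.11 |
| 1 | 0.14 | 0.21 |
| 2 | 0.31 | 0.53 |

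The table shows only that an uncontrolled pre-post test is sensitive to small systematic shifts that format masking cannot remove. It is not evidence that any such shift will occur, and it does not measure the effect of losing format blinding.

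**The case against.** The case on the other side has real weight.

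**The sentence is partly sound.** It covers entry and analysis as well as collection, and both can be masked by coding. A reader might infer that there is no blinding at all, or that only laboratory results can be masked. The documents support neither. Nor do they say that assessors are told which site has which format. Masking of on-site staff is implausible and undescribed, not proven absent. This stands and limits the point.

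**The measurements leave little room for judgement.** Weight comes from an electronic calibrated scale, blood pressure from an automatic monitor and activity from accelerometers, and "All anthropometric measures will be taken in duplicate and averaged". This largely stands. Averaging duplicates reduces random error but not a shift shared by both readings, and height and waist depend more on the operator than scale weight does.

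**The protocol claims blinding to allocation, not to visit.** That is correct: it nowhere says that blinding protects the pre-post test. The warning is about what readers may credit to the sentence. A reader might also infer that assessors see earlier values at follow-up; nothing in the article says so.

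**A tempting size does not belong here.** For an assumed child of 145 cm at 140% of median BMI, a 0.5 cm height shift gives 1 − (145/145.5)² = 0.69% of BMI. That is 0.0069 × 140 ≈ 0.96 points of overweight, or 22% of the 4.3-point planning effect. But 0.5 cm is an assumption, five times the 0.1 cm recording unit. To bias the mean by that much it would have to run in the same direction in essentially every child, at follow-up only. It also illustrates bias related to the visit, not lost format blinding, so it should not be read as the size of this defect.

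**Detail may sit in a fuller document.** The article mentions a written procedure for data collectors that is not shown. That would excuse a missing description of masking, but the point rests on statements in the article that do not fit together.

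**Conclusion.** The point holds for on-site data collectors, including those who measure height and weight for the primary outcome: they cannot credibly be called blinded to format. It does not extend to laboratory assays, data entry or analysis, where masking is feasible. It is also true that intact format masking would not protect the pooled, uncontrolled pre-post primary test against a shift common to both sites.

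The consequence is modest. The primary measure is largely objective, and the comparison that format blinding mainly protects is exploratory. No numerical size can be derived from the documents. The conclusion assumes that the Research setting section's statement about assessment at the sites includes anthropometry, which is its natural reading. The sentence should be corrected because it states a property that the design does not provide, and the correction is cheap.

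**What to change.** 1. Limit the blinding sentence to laboratory, data-entry and analysis staff, and say how it is achieved: coded participant IDs and site codes, with mobile-use records held separately from the outcome dataset while analysts are masked.
2. State that on-site assessors are not assumed blinded to format.
3. Do not cite blinding, here or in the results paper, as protection for the pre-post result.
4. As a safeguard suited to a pre-post design, record the duplicate 12-week and 24-week measurements on forms that do not show earlier values.

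**Cost:** items 1 to 3 are wording and coding, and item 4 is a change of form layout. No extra children or staff are needed, and the planned tests do not change. The one small downside is that implausible changes from earlier values must be caught at data entry rather than at the visit.

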### Statistical analysis

Outcome measures will be stratified by delivery format to assess whether the mobile technology-supported delivery of the intervention is as efficacious as the face-to-face format. Descriptive statistics for change in endpoints (mean, median, and standard deviation) between baseline and 12-week measurements will be computed separately for each program format (face-to-face or hybrid mobile technology-supported program). The statistical significance of the change at 12 weeks will be assessed using a paired t-test combining both formats. One-sided statistical tests will be used, as the interventions approaches are of interest only if they decrease the percentage overweight and lead to improvements in diabetes risk factors. Statistical significance is set at alpha = 0.05. Sample size constraints do not allow adequate statistical power to formally test for differences between the two formats. However, exploratory models using linear regression analysis will estimate the magnitude of the difference between the face-to-face and combined formats, adjusted for baseline levels and the potential correlation between the participants within a given YMCA (expected to be small). These parameter estimates will provide effect sizes to appropriately power a larger study comparing the two formats. Since this is a randomized comparison, confounding is not an issue as long as there is non-differential dropout between the two formats. Differential dropout between the two formats will be assessed using a Fisher’s Exact Test. Similar analyses will assess whether improvements are maintained after the intervention ends, by comparing the 24-week versus 12-week values. We acknowledge the potential for differential loss to follow-up and missing data. Baseline values of those who complete the study versus those who do not will be compared using two sample independent t tests and Fisher’s Exact Tests, as appropriate. Additional sensitivity analyses will use multiple imputation for missing values and an intent-to-treat analysis with baseline values carried forward.

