### Intervention delivery

The intervention will be conducted over 12 weeks at two YMCA locations. Each location will engage up to thirty children and their parents. The program duration is informed by the length of the YMCA adult-focused Diabetes Prevention Program, as well as studies in adults [31, 32] and children [33] that suggest success in weight loss and behavior changes during the first 8 to 12 weeks of a program predict overall success. Each Y location will host up to three concurrent intervention groups (each comprised of no more than 10 families) led by two YMCA Lifestyle Coaches. Program activities will occur at times convenient to parents (typically, early evening or weekend). All activities will promote active learning (i.e., hands-on activities requiring movement, interaction) and provide opportunities to build and practice skills related to healthy eating and physical activity as a family. For participants in the hybrid intervention, content will consist of equivalent topics and activities as the face-to-face sessions, made accessible through the study website (Moodle Pty Ltd, Perth, Australia) and a study-provided mobile device (Kindle Fire HDX7, Amazon).

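### The primary paired t-test and the sample size treat about 48 children as independent, although they are treated in about six coach-led groups

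*Protocol article*

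**What the plan says.** **Test.** The Statistical analysis section of the protocol article fixes the main test: "The statistical significance of the change at 12 weeks will be assessed using a paired t-test combining both formats". It is one-sided at 0.05. Correlation between participants appears only later in that section, for the exploratory regression that compares formats. It is defined there by YMCA, and the authors anticipate little of it.

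**Size.** Sample size and power states that "The primary outcome is change in percent overweight". The planning effect comes from a cited YMCA-based study that "observed a mean decrease of 4.3 % in percentage overweight (SE = 1.1"). The number of children "is based on the number of participants needed to detect an effect size of this magnitude with" 80% power, one-sided at 0.05, and then: "Given a final sample of 48 children and allowing for up to 20 % attrition, 60 participants will be recruited". No ICC or design effect is mentioned.

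**Delivery.** Intervention delivery says each location hosts "up to three concurrent intervention groups (each comprised of no more than 10 families) led by two YMCA Lifestyle Coaches". Study design recruits 30 families per format, with one site per format. The coach training section plans for twelve coaches.

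**The concern.** A paired t-test on 48 changes takes the children as 48 independent observations and uses 47 degrees of freedom. The design gives reason to doubt that. Children in a group share two coaches, a timetable and the other families, and the weekly format in Table 2 deliberately has families exchange experiences and ideas. If changes within a group tend to move together, the mean change varies more than the test assumes. Its p-value is then too small, and the power calculation, which makes the same assumption, is too favourable.

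The plan's one acknowledgement of correlation does not reach the primary test. It also names the site rather than the coach-led group. With one site per format, a site effect cannot be separated from the format effect.

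The comparison has no untreated control and the test is already one-sided, so there is little room for further false-positive risk.

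**Working it through.** **Inputs from the article.** Effect 4.3; SE 1.1 in the cited study (neither its n nor an SD is given); one-sided alpha 0.05; power 80%; 48 completers; 60 recruited.

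**Number of groups.** Thirty families per site at no more than 10 per group needs at least three groups, and three is the stated maximum of concurrent groups. Twelve coaches in pairs also gives 12 / 2 = 6. Completers per group: 48 / 6 = 8.

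**Assumption.** The ICC of 12-week change within a coach-led group is not in the article; 0.01 to 0.10 is shown.

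**Step 1: the plan's own figures.**
- Attrition: 48 / (1 − 0.20) = 60, which reproduces.
- The 80% cannot be checked, because an SE without its n gives no SD. Solving the one-sample t-test for 80% power at n = 48 gives an SD of about 11.8 (standardised effect 4.3 / 11.8 = 0.364). That would require about (11.8 / 1.1)² ≈ 115 children in the cited study.
- If SE 1.1 were instead the SE at n = 48, the SD would be 1.1 × √48 = 7.6 and power 98.6%.

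**Step 2: effect of grouping.**
- Design effect DE = 1 + (8 − 1) × ICC; effective n = 48 / DE.
- True SE / assumed SE = √DE (approximately).
- True one-sided error of the planned test ≈ 1 − Φ(1.645 / √DE).
- Power comes from the noncentral t with noncentrality 4.3 / (SD × √(DE / 48)).

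With SD 11.8:

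| ICC | DE | Effective n | True error of planned test | Power, 47 df | Power, 5 df | Power, 4 df |
|---|---|---|---|---|---|---|
| 0 | 1.00 | 48.0 | 5.0% | 80% | 70% | 67% |
| 0.01 | 1.07 | 44.9 | 5.6% | 78% | 67% | 64% |
| 0.02 | 1.14 | 42.1 | 6.2% | 75% | 65% | 62% |
| 0.05 | 1.35 | 35.6 | 7.8% | 69% | 59% | 56% |
| 0.10 | 1.70 | 28.2 | 10.4% | 60% | 51% | 48% |

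The 47-df column shows the design effect alone. The 5-df column is a t-test on six group means. The 4-df column is the same with a term for delivery format.

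Simulating six groups of 8 (200,000 trials) gives a true error for the planned test of 5.6%, 6.2%, 7.9% and 10.3% at ICC 0.01, 0.02, 0.05 and 0.10. In a separate run of 100,000 trials the t-test on group means stayed at about 5%.

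**Step 3: dependence on the SD.** With SD 7.6 and ICC 0.01, 0.05 and 0.10, power is 98%, 95% and 91% with 47 df; 94%, 89% and 82% with 5 df; and 92%, 86% and 79% with 4 df.

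**The case against.** The other side has several fair points.

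- **The ICC is assumed.** The article's only remark is that correlation within a YMCA should be slight. At ICC 0.01 the true error is about 5.6% and the design effect costs about 2 points of power. This stands as a limit on size; it does not change the direction.
- **The SD is unknown.** The 11.8 is back-calculated from the 80%. A reader might infer that the trial is underpowered, but the article does not support that: with SD 7.6, power remains above or very near 80% throughout.
- **The power loss has two sources.** A reader might attribute the whole fall from 80% to 51–67% to correlation. A 5-df test has only 70% power even at ICC 0, so about 10 points are the price of having few groups.
- **Shared exposure differs by site.** Hybrid families receive five of the twelve sessions on a tablet and so meet face to face for seven. One ICC for all groups is a simplification.
- **Six is inferred.** Recruitment and coach training each run in two rounds, so more and smaller groups are possible. That would reduce the design effect and add degrees of freedom.
- **The trial is partly preparatory.** Its estimates are meant to help size a larger study. It nevertheless sets a formal significance test at one-sided 0.05, so the validity of that test still matters.

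None of these supplies an allowance for group in the primary test or in the sample size.

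**Conclusion.** The concern holds in a limited form. Both the primary test and the sample size assume independent children, while the article describes treatment in about six coach-led groups. For any positive group ICC the primary standard error is too small; this does not depend on the SD. With six groups of 8 and ICC 0.01 to 0.10, the true one-sided error is about 5.6% to 10%.

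The loss of power is conditional. It applies if the plan's 80% at 48 children, and hence an SD of about 11.8, is accepted, and the few-groups penalty must be counted separately from the correlation.

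This should be fixed. Confidence in the direction is high; confidence in the size is moderate, because neither the ICC nor the SD is given.

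**What to change.** Make the primary test of the 12-week change account for coach-led group. One form is a linear mixed model with a random intercept for group, delivery format as a centred fixed effect, and small-sample degrees of freedom (Kenward-Roger or Satterthwaite). An equivalent analysis of the group means would also do. Format belongs in the model because otherwise any difference between formats or sites enters the between-group variance. The paired t-test can stay as a secondary analysis.

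In Sample size and power, state the assumed SD and its source, and give power over a range of group ICCs with the expected number of groups, keeping 60 children.

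The cost is a less favourable stated power and a larger standard error. Group membership is known by design, so no extra children or measurements are needed. A benefit is an estimate of the group ICC, though imprecise from six groups, for the larger study that the article has in view.

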### Participants

Eligible participants are 9 to 12-years-old at study enrollment, have a BMI at or greater than the 85th percentile for age and sex, and have one or more of the following T2D risk factors: ethnic minority, first or second degree relative with T2D, conditions associated with insulin resistance or metabolic syndrome (including acanthosis nigricans, hypertension, dyslipidemia, polycystic ovarian disease, small for gestational age birth weight, maternal history of gestational diabetes [17]). Eligible children must also have a primary caregiver willing to participate in intervention sessions and activities (note: primary caregiver is an adult who most frequently prepares/obtains food, regulates media use, and provides physical activity opportunities for the child), be willing to use a study-provided mobile device throughout intervention, and speak and read English. Exclusion criteria are previously diagnosed Type 1 or Type 2 diabetes mellitus (this is not an exclusion criteria for the caregiver), psychiatric disturbances or mental illness, limitations preventing physical activity, or using medications known to cause weight loss or gain or affect appetite.

Participants will be recruited through pediatric and family medicine practices, the Southern Arizona YMCA membership, and the Tucson community (e.g., libraries, community centers, public health department, and local health fairs) using electronic announcements, flyers, posters, and word-of-mouth between May and August 2015, and between October 2015 and January 2016. Respondents will be invited to attend study information sessions held at participating YMCA locations where eligibility will be confirmed. Interested and eligible respondents will complete the informed consent process following University of Arizona Institutional Review Board-approved materials and methods and assigned a study location based on geographical proximity. Written consent will be obtained from parents; verbal assent will be obtained from youth and documented in writing by study staff. Families who are not yet YMCA members will be provided access to YMCA facilities free of charge for the duration of the study, with an opportunity to continue at a reduced rate after the study has concluded.

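### The only powered test is a pooled, uncontrolled pre-post change, so it cannot show the programme impact that the objectives and the design statement claim

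*Protocol article*

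**What the plan says.** All references are to the protocol article.

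- **Outcome.** Sample size and power: "The primary outcome is change in percent overweight". The Data collection section defines it as percentage over the median BMI for age and gender.
- **Test.** Statistical analysis: "The statistical significance of the change at 12 weeks will be assessed using a paired t-test combining both formats". The test is one-sided ("One-sided statistical tests will be used, as the interventions approaches are of interest only if they decrease the percentage overweight"), and "Statistical significance is set at alpha = 0.05". The Abstract gives the same paired test.
- **Arms.** Study design and Randomization: two YMCA sites, one per format, 30 families each. Both sites deliver the programme. No untreated or delayed group is described.
- **Randomised contrast.** Statistical analysis says that the sample is too small to test the formats against each other formally. That comparison is left to exploratory regression.
- **Claim.** The second objective, at the end of Background, is worded as a test of the programme's impact on child outcomes. Study design says: "The impact of the EPIC Kids intervention will be evaluated using a group-randomized, non-inferiority trial design".
- **Entry.** Participants: BMI at or above the 85th percentile for age and sex, plus a diabetes risk factor, with a caregiver willing to take part. Recruitment runs May to August 2015 and October 2015 to January 2016.

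**The concern.** The claim and the test do not match. Impact means change compared with what would have happened without the programme. The pooled paired test compares each child with that child's own baseline, and every child receives the programme. Randomisation decides only which format a child's site delivers, so it adds nothing to this test.

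The test therefore credits the programme with any average movement over 12 weeks. Children are selected on BMI, which is the basis of the outcome scale, so some regression to the mean is possible. Season, the motivation of volunteering families and background trends may also act. Nothing in the article limits the pooled result to a descriptive reading or names these alternatives. The remark in Statistical analysis that confounding is not an issue refers to the format comparison and does not protect the pooled test. Background itself criticises community studies for often lacking comparison groups.

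At stake is what the trial may conclude. A p-value below 0.05 would be reported as programme impact and used to support scaling up, and this contrast cannot bear that reading.

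**Working it through.** **1. The plan's own figure.** Inputs from Sample size and power: target fall 4.3 points (source SE 1.1), one-sided alpha 0.05, power 80%, 48 analysed, 20% attrition.

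- Recruitment: 48 / (1 − 0.20) = 60. This reproduces.
- The 48 cannot be checked directly, because neither the SD of change nor the sample size behind the SE is given. Solving for the SD under a one-sided paired test: SD = 4.3 × √48 / (1.645 + 0.842) = 12.0 by the normal formula, or 11.8 by the noncentral t. The source study would then have had about (11.8 / 1.1)² ≈ 115 children.

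So 48 fits a paired test if the SD of change is about 11.8. That SD is back-solved, not stated.

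**2. What the test needs in order to reject.** The critical t on 47 degrees of freedom is 1.678, so the smallest significant mean fall is 1.678 × 11.8 / √48 = 2.86 points.

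**3. Effect of a fall not due to the programme.** If the programme does nothing but the mean falls by δ for other reasons, the rejection probability comes from the noncentral t with 47 degrees of freedom and noncentrality δ√48 / SD. Both δ and SD are assumptions.

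| Assumed δ (points) | SD 8 | SD 10 | SD 11.8 |
|---|---|---|---|
| 0 | 5% | 5% | 5% |
| 0.5 | 11% | 10% | 9% |
| 1.0 | 21% | 17% | 14% |

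A δ in the other direction would lower the rejection rate below 5% and could hide a real effect.

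**4. Is a δ of this order plausible from regression to the mean alone?** Under normality it equals (1 − r) × k × population SD, where r is the retest correlation and k is how far the selected mean lies above the population mean, in SDs. Assume a population SD of 15 to 20 points and r of 0.95 to 0.99.

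- If the 85th percentile cut off the top 15% of these children, k = 1.55, giving 0.01 × 1.55 × 15 = 0.23 up to 0.05 × 1.55 × 20 = 1.55 points.
- Background says nearly one-third of U.S. children are overweight, and Discussion puts 18% of 6- to 11-year-olds at or above the 95th percentile. The percentile is thus a reference cut-off that far more than 15% exceed. With one-third above it, k = 1.09, giving 0.01 × 1.09 × 15 = 0.16 up to 0.05 × 1.09 × 20 = 1.09 points.

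The second range fits the article better. It shows only that the drifts in step 3 are not far-fetched. It is not an estimate for this trial.

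**The case against.** The other side has several sound points.

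- **Design choice, openly stated.** The pooled test and the lack of power between formats are disclosed. Feasibility is an objective, and the article looks ahead to a larger study. This stands: the lack of a control is not an error, and none is asked for here. But the remark about powering a larger study concerns the format contrast and does not qualify the impact wording.
- **Direction is unknown.** A reader might infer that selection, season and motivation all push towards a fall. The article does not support that. It gives recruitment windows, not measurement dates, and no sign or size for season or motivation.
- **Baseline may already be separate.** A reader might infer that the eligibility measurement doubles as baseline. The article does not say so. Participants describes "study information sessions held at participating YMCA locations where eligibility will be confirmed", while Data collection describes baseline as its own time point with duplicate, averaged measures. If they are separate, much of the short-term measurement error drops out and regression to the mean may be small.
- **Efficacy is a framework label.** A reader might take the Process evaluation section to say that the pooled test proves efficacy. There, efficacy is a RE-AIM dimension that also covers feasibility, attrition and delivery fidelity. In Statistical analysis the word belongs to the format comparison.
- **The outcome is age- and sex-referenced.** This removes much of expected growth, but not the other alternatives.

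These points limit the size of the problem. They do not supply the missing comparison, and the impact wording in the second objective and in Study design remains.

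**Conclusion.** The point holds as a mismatch between claim and test. The only powered analysis is a one-sided, pooled, within-child comparison with no unexposed group. It uses neither the group randomisation nor a non-inferiority comparison, so it can show that percent overweight changed during the programme but not that the programme changed it.

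How far this could mislead cannot be fixed from the article. At n = 48 and the back-solved SD of 11.8, assumed non-programme falls of 0.5 and 1.0 point give rejection rates of about 9% and 14% instead of 5%. A smaller SD makes this worse. The conclusion about attribution does not depend on these assumptions; only the illustration does. The stronger readings, that the bias is known to favour the programme or that the sample size is wrong, are not supported.

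**What to change.** 1. Reword the second objective, the opening of Study design and the Statistical analysis section so that the pooled result is a preliminary within-group change in percent overweight during the programme, reported as an estimate with a confidence interval and not attributed to the programme.
2. State that randomisation bears only on the exploratory format contrast, not on the pooled test.
3. Name regression to the mean after selection on BMI, and secular or seasonal change, as limits on the pooled result. Mention volunteer effects with them.
4. Keep efficacy in the Process evaluation section as the RE-AIM label, and add that the pooled test does not establish it.

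The cost is wording only: no new data, no change in sample size and no control arm. The downside is a weaker headline claim.
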